### Randomization/assignment of interventions

Recruited patients will only be randomized on the day of surgery if the clinical team places an order with the blood bank for platelet transfusion to treat active bleeding during the first 6 h after termination of CPB, and both platelet types are available (Fig. 1). When the platelet order is received, the blood bank technologist or assigned research coordinator will confirm the patient has consented to the study and is enrolled in the trial. The patient will then be randomized and the assigned product will be released [18, 24].

Patients will be randomly assigned (1:1 ratio) to study groups on the day of surgery using a permuted block, stratified (by center) allocation scheme prepared by a biostatistician not involved in the trial. Sequentially numbered sealed envelopes based on the randomization lists will be provided to the blood banks that will be providing the platelet product. This process, which has been successfully used in previous similar studies [25–28], has the advantage of allowing the technologists or coordinators to randomize patients as soon as the order is received without delaying therapy. The spot in the randomization list will not be reused if the patient assigned to it does not receive the platelet product. Once the order for the first platelet product is received and eligibility has been confirmed, the blood bank technologist will open the randomization envelope, and prepare and release the assigned platelet product in tamper-proof, temperature-stable containers that have been validated for this purpose and will be identical for each study arm. To maintain blinding, thermal gloves will be released by the blood bank for product handling and the product label (containing collection and expiration dates and type of platelet) will be obscured.

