### Interventions

Patients randomized to the room temperature platelet (RTP) group will receive ABO-identical, pathogen-reduced via INTERCEPT [29], buffy-coat platelets in platelet additive solution maintained at 22 °C for up to 7 days, as per the current standard of care.

Patients randomized to the delayed cold-stored platelet (DCSP) group will receive up to two doses of ABO-identical, pathogen reduced via INTERCEPT, buffy-coat platelets in platelet additive solution maintained at 22 °C for up to 4 days (with agitation) then placed in cold-storage (at 1–6 °C, without agitation) for a minimum of 24 h, with expiration at 14 days after collection.

The duration of treatment is from the initiation of the first platelet transfusion up to 24 h after CPB or receipt of two doses of the product, whichever occurs first. There will be no other changes to participants’ pre-and post-operative management.

The clinical team will then administer the platelets only if the following criteria are met: [23, 30] (a) bleeding is severe enough to necessitate treatment (Bleeding Severity Scale Moderate or higher [31] or chest tube output ≥ 200 mL/h for any 1 h or ≥ 2 mL/kg/h for 2 consecutive hours in the first 6 postoperative hours [32]; (b) heparin is adequately reversed (confirmed by the return of post-protamine activated clotting time [ACT] to within 15% of baseline ACT); and (c) presence of thrombocytopenia (total platelet count < 100,000 × 10^6^) or platelet dysfunction (functioning platelet count < 75,000 × 10^6^ in response to collagen activation, as measured by the point-of-care platelet function assay PlateletWorks currently in use at both sites). Patients can also be treated irrespective of the platelet count or function if bleeding is deemed to be life-threatening, in accordance with institutional coagulation management algorithms for massive bleeding previously validated by our group [23]. Once the decision is made to administer platelets, the administering clinician will put on the insulated gloves provided, retrieve the product from its sealed temperature-controlled container, carry out routine checks, and administer according to usual care including in-line filtration tubing (170–260 µm) primed with normal saline.

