#### Secondary patient-centered outcomes

(i) mean number of allogeneic blood components (ABCs) transfused (including red blood cells, plasma, and platelets) within 24 h of CPB end, with each platelet recorded as 3.5 units based on donor exposure (as 2 buffy coat platelets prepared from 7 donors), (ii) mean number of ABCs within 7 days of CPB, (iii) total number of coagulation factor products administered (fibrinogen concentrate, prothrombin complex concentrates, and activated recombinant factor VII) within 24 h and 7 days of CPB, (iv) incidence of severe to massive bleeding (using a modification of the universal definition of perioperative bleeding [UDPB] in cardiac surgery, and its individual components [34, 35]) within 24 h of CPB, (v) chest tube drainage at 12- and 24-h after chest closure, (vi) total platelet count with a functional platelet count (PlateletWorks) at preoperative baseline, at the time of rewarming on CPB, immediately after CPB at protamine reversal, within 60 min before first product administration, and within 60 min after first product completion, and (vii) changes in international normalized ratio (INR), prothrombin time (PT), activated partial thromboplastic time (aPTT), fibrinogen activity, rotational thromboelastometry (ROTEM) EXTEM clotting time (CT) and maximum clot firmness (MCF), ROTEM FIBTEM MCF and thrombin generation, from within 60 min before to within 60 min after the initiation of the first product administration, (viii) EQ-5D-5L version of EQ-5D™ questionnaire [36] was collected at baseline and at postoperative day (POD) -30, and (ix) case-costing data for each patient.

Additional safety outcomes include (i) incidence of serious treatment-emergent adverse events (AE) from the start of surgery to POD-30, (ii) incidence of thromboembolic events from randomization to POD-30, (iii) duration of ventilation and ventilator-free days up to POD-30, (iv) duration of intensive care unit (ICU) stay up to POD-30, (v) duration of hospitalization up to POD-30, (vi) incidence of death up to POD-30, and (vii) days alive and out of hospital at POD-30.

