### Statistical analysis

For the statistical analysis of the efficacy parameters, the following analysis sets will be considered:

The intention to treat (ITT) population: all randomized patients who receive at least a whole or parts of an IMP dose, irrespective of the number of IMP doses received. We anticipate that ≥ 90% of randomized patients will receive the first dose of IMP. Should a patient receive IMP that is not in concordance with the randomization schedule, the treatment group will be defined according to the randomization (rather than the actual treatment received). The primary outcome and mortality for non-consenting patients will be collected from as many sites as possible, as permitted by the local REB.

The per-protocol (PP) population: all patients in the ITT sample, excluding patients with major protocol deviations. Patients meeting any of the following criteria will be excluded.Patients who do not receive at least 80% of the first platelet dose to which they were randomizedPatients receiving treatment not in concordance with the randomization schedulePatients who significantly violate inclusion/exclusion criteria (e.g., did not have cardiac surgery with CPB, randomized after POD-3, etc.)

The restricted safety population (safety analysis set): all patients who receive at least one whole or parts of the first platelet dose (i.e., the ITT population).

A final decision about the classification of protocol deviations as major and minor and their consequences regarding the assignment of patients to analysis populations will be made during the blinded data review meeting prior to unblinding for the final analyses by the lead PI.

The ITT analysis sample is considered the primary sample for analysis of the primary endpoint. The evaluation of the primary endpoint will additionally be performed for the PP sample.

The data will be analyzed using protocols established for safeguarding privacy and confidentiality. These include password-protected computers, locked file cabinets for hardcopies, and no public discussion of individual cases. There will be no linkages to other datasets, and no disclosures of person identifiers. Reports will present aggregate statistics only.

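### Serious treatment-emergent events are counted from the start of surgery, before randomization and the first dose; separately, two post-dose laboratory samples are timed from different events

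*Protocol article*

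**What the plan says.** **Serious events.** Under Secondary patient-centered outcomes, the first additional safety outcome is the "incidence of serious treatment-emergent adverse events (AE) from the start of surgery to POD-30". The second is the "incidence of thromboembolic events from randomization to POD-30".

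**Randomization and treatment.** Randomization/assignment of interventions randomizes a patient only once the team orders "platelet transfusion to treat active bleeding during the first 6 h after termination of CPB". Interventions defines the treatment period: "The duration of treatment is from the initiation of the first platelet transfusion up to 24 h after CPB", or until two doses have been given if that comes sooner.

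**Safety set.** Statistical analysis restricts the safety population to patients who received all or part of a first platelet dose.

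**Schedule.** Table 1 has separate rows for AEs and SAEs and for treatment-emergent events. Both are marked at POD-1, POD-7 or discharge, and POD-30. Neither is marked in the Surgery column.

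**Laboratory samples.** Secondary outcome (vi) takes the last platelet count "within 60 min after first product completion". Secondary outcome (vii) measures change in INR, PT, aPTT, fibrinogen, ROTEM and thrombin generation "from within 60 min before to within 60 min after the initiation of the first product administration".

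**The concern.** An event can be treatment-emergent only if it starts or worsens after treatment begins. Here treatment begins after bypass, possibly hours after, so a count that opens at the start of surgery includes events that no study product could have caused. Such events are the same in expectation in both arms. They do not favour either arm, but they add background that makes a real difference harder to see.

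The neighbouring thromboembolic item opens at randomization. Taken at its word, the list puts a stroke during bypass inside the serious-event count and outside the thromboembolic count.

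The laboratory point is separate and smaller. A coagulation sample drawn while the product is still running satisfies (vii) but reflects only part of the dose. It also need not be the draw used for the platelet count in (vi). The two sets of results would then describe different amounts of product.

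**Working it through.** The plan states no figure on this point, so there is none to reproduce. The check compares the time anchors and then illustrates the size with assumed rates.

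**1. Order of events in a randomized, treated patient**

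| Step | Source section | Serious-event window | Thromboembolic window |
|---|---|---|---|
| Surgery starts | Secondary patient-centered outcomes | opens | – |
| Bypass runs and ends | Randomization/assignment of interventions | open | – |
| Platelet order within 6 h, randomization | Randomization/assignment of interventions | open | opens |
| First platelet transfusion, treatment starts | Interventions | open | open |
| POD-30 | Secondary patient-centered outcomes | closes | closes |

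The serious-event window is open for the first three steps, before any study product is given. The safety set holds only treated patients, but nothing in that definition removes the events they had before treatment.

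**2. Size of the dilution**

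Let q be the risk of a serious event between the start of surgery and the first dose, equal in both arms. Let p be the risk after the first dose, and assume the two are independent within an arm. Then

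observed risk = 1 − (1 − q)(1 − p)

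and the difference between arms is

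[1 − (1 − q)(1 − p₁)] − [1 − (1 − q)(1 − p₀)] = (1 − q)(p₁ − p₀).

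The documents give no event rates, so p₁ = 20%, p₀ = 10% and all values of q are assumptions.

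| q | Observed, higher-risk arm | Observed, lower-risk arm | Difference (points) | Ratio |
|---|---|---|---|---|
| 0 | 20.0% | 10.0% | 10.0 | 2.00 |
| 5% | 1 − 0.95 × 0.80 = 24.0% | 1 − 0.95 × 0.90 = 14.5% | 9.5 | 1.66 |
| 10% | 1 − 0.90 × 0.80 = 28.0% | 1 − 0.90 × 0.90 = 19.0% | 9.0 | 1.47 |
| 15% | 1 − 0.85 × 0.80 = 32.0% | 1 − 0.85 × 0.90 = 23.5% | 8.5 | 1.36 |

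Statistical analysis plans differences in means or percentages, so the difference column is the relevant one. The loss is 0.5 to 1.5 points.

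**3. The loss against sampling error in the pilot**

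With 25 patients per arm (50 randomized 1:1) and the same assumed risks, the standard error of the difference is √(0.20 × 0.80/25 + 0.10 × 0.90/25) = √(0.0064 + 0.0036) = 0.10, or 10 points. The dilution is small beside it.

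**4. The two laboratory windows**

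Both samples are allowed 60 minutes. For (vi) the clock starts when the first product has finished; for (vii) it starts when the product is begun. If a dose takes d minutes, the part of the (vii) window that precedes completion is d/60, up to all of it. The documents give no infusion time. If d were 30, half the window would precede completion (30/60); if d were 60, all of it would (60/60). These are shares of the permitted window, not of samples: they do not show when samples will actually be drawn.

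**The case against.** **The term itself may be the filter.** On this reading, treatment-emergent selects the events and the dates only describe surveillance. Table 1 lends support, with separate rows for the two kinds of event and no mark under Surgery, and an operational definition may sit in the full protocol or SAP. The reading is possible, but it leaves the start-of-surgery anchor with no function. The article would still hold two instructions that can be followed differently.

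**This is a feasibility pilot.** The primary endpoints are feasibility measures, and Statistical analysis disclaims formal inference on the clinical outcomes. That stands and limits the weight of the point. A reader might infer that the window biases a non-inferiority claim on safety, because a diluted difference is easier to pass. The documents do not support that for the pilot: non-inferior safety is the hypothesis of the future trial, and no safety margin or test is shown.

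**The ratio overstates the effect.** The fall from 2.00 to 1.36 looks dramatic, but the plan names differences, not ratios, and the rates are assumed. This stands.

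**Randomization is a sound start for thromboembolic events.** This also stands. A reader might take the mismatch between the two safety items as an error in both. Only the serious-event item is at fault, since randomization is a legitimate origin for comparing the arms.

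**One draw can serve (vi) and (vii).** True, if the product finishes within the hour and the sample follows completion. Table 1 also lists platelet count and coagulation profile under the same administration column. It would go too far to say that the coagulation results will understate the effect of a dose; the text shows only that (vii) permits a sample before the dose is finished.

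**Conclusion.** The concern holds at modest size. As written, the serious-event outcome opens before randomization and before treatment, contrary to its own label and to the article's definition of the treatment period, and differently from the thromboembolic item beside it.

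The consequence is mislabelling and dilution by (1 − q), with no push towards either arm. In the illustration a 10-point difference loses 0.5 to 1.5 points. That rests on assumed event rates, equal pre-dose risk in the two arms, and independence of pre-dose and post-dose events.

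The laboratory anchors in (vi) and (vii) differ without a stated reason, and (vii) can capture an incomplete dose. Its frequency cannot be judged without an infusion time.

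Neither point affects the pilot's feasibility decisions. They are worth correcting because Design and Statistical analysis provide for the pilot's outcome data, including safety, to join the definitive trial's dataset if that trial goes ahead. An unclear definition would go with them.

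**What to change.** - **Serious events:** count those that start or worsen from initiation of the first study platelet dose to POD-30. List serious events between the start of surgery and that dose separately, as pre-treatment.
- **Thromboembolic events:** keep randomization as the start.
- **Outcome (vii):** time the post-dose coagulation sample within 60 min after completion of the first product, as in (vi), so that one draw can serve both.

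**Cost.** A small protocol amendment. The serious-event change is one of definition and needs event onset and first-dose times to be recorded. The change to (vii) alters the timing of a study procedure, so it is more than wording, but it adds no sample. Ethics and dissemination sends amendments to the REB and Health Canada and has them communicated to the IDSMC, registries and participants. Because recruitment was due to begin in 2024, samples already drawn under the present (vii) wording should be identifiable by their timing relative to completion, where those times were recorded.

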In the pilot study, we will estimate rates and percentages for feasibility outcomes, along with lower one-sided 95% CIs where high percentages are desirable (e.g., enrollment rate) and upper one-sided CIs where low percentages are desirable (e.g., loss to follow-up, protocol deviations). Point estimates will be compared to our predetermined targets to make decisions on feasibility and the need for changes to the protocol.

Although this study will make no formal inferences on the definitive trial's primary and secondary outcomes, we will present outcomes in tables and graphs (e.g., a histogram for DAOH-30). The differences in means or percentages between the intervention and control groups will be estimated, along with a parametric or bootstrapped (for DAOH) 95% CIs.

The feasibility outcomes of the pilot study will inform the conduct of the definitive trial. Specifically, if all 3 of our primary feasibility outcomes are achieved, we will proceed to a larger trial with minimal or no protocol modifications. If only a portion of our primary feasibility outcomes are achieved, we will hold an investigator meeting and ascertain what aspects of the protocol should be modified, and if a second pilot trial is required in the face of significant protocol modifications prior to proceeding with a larger trial. If none of our primary feasibility outcomes are achieved, we are unlikely to be able to proceed with a larger trial [33, 38]. If we proceed to the definitive trial, all outcome data derived from the pilot study pertaining to the definitive trial’s primary, secondary, and safety outcomes will contribute to the definitive trial's dataset.

No interim analysis will be conducted. We will assess enrollment, randomization, and treatment rates by sex and institution but, because of the small sample size, analyses of the pilot study will not examine subgroups. In the main study, heterogeneity of treatment effect will be assessed by examining possible interaction effects by sex (male/female) and surgical complexity (simple/complex surgery).

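### Raw ICU, hospital and ventilation durations compared as means can read an early death as a short stay, and ICU stay alone has no death-inclusive companion

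*Protocol article*

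**What the plan says.** All of this is in the protocol article. Under Secondary patient-centered outcomes, the additional safety outcomes include:

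- "duration of ventilation and ventilator-free days up to POD-30"
- "duration of intensive care unit (ICU) stay up to POD-30"
- "duration of hospitalization up to POD-30"
- "incidence of death up to POD-30"
- "days alive and out of hospital at POD-30"

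Serious treatment-emergent adverse events and thromboembolic events are in the same list.

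Under Statistical analysis, the comparison is given once for all outcomes: "The differences in means or percentages between the intervention and control groups will be estimated". Intervals accompany these estimates and are parametric, except that DAOH has a bootstrapped one. The same section disclaims formal inference on the definitive trial's outcomes. It also says that pilot data on those outcomes, safety outcomes included, will enter the definitive dataset if that trial goes ahead.

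Table 1 schedules ventilation time, ICU stay, hospital stay and all-cause mortality.

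**The concern.** ICU stay, hospital stay and ventilation time all stop when the patient dies. Unless something else is specified, a patient who dies on day 1 contributes one day, which is shorter than most survivors contribute. In a difference of means, that death moves its arm in the direction that a reader takes as benefit. This is the wrong direction for a safety outcome.

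The Discussion names thromboembolism as the possible hazard of cold-stored platelets, while calling the risk largely theoretical. The Background sets out a hypothesis of non-inferior safety. A measure that improves when patients die early is anti-conservative for that hypothesis.

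The outcome list itself shows where the protection stops. Ventilation time is paired with ventilator-free days, and hospital stay sits beside DAOH. ICU stay has neither kind of partner, and DAOH cannot stand in for one because it does not separate ICU days from ward days.

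**Working it through.** The article states no mean stay, standard deviation or death rate, so there is no planned figure to reproduce. The check is whether the mechanism works, and in which direction.

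**Inputs from the article.** n = 22 evaluable or 25 randomized per arm (Determination of sample size; 1:1 allocation); 30-day horizon.

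**Assumed inputs.** Survivors' stay L = 8 to 10 days; k = 1 to 3 extra deaths in one arm, all in hospital, on day d = 1 or 2.

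**Formulas.**

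- Mean stay in the arm: ((n − k)·L + k·d)/n, so the change from no deaths is −k(L − d)/n.
- Mean DAOH to day 30: (n − k)(30 − L)/n, so the change is −k(30 − L)/n. A patient who dies in hospital on day 1 or 2 has no days alive out of hospital, so no special scoring rule is needed here.

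**Hospital stay, n = 22, L = 8, d = 1.**

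| Deaths | Mean stay | Change in stay | Change in DAOH |
|---|---|---|---|
| 0 | 8.00 | – | – |
| 1 | (21×8 + 1)/22 = 7.68 | −0.32 | −22/22 = −1.00 |
| 2 | (20×8 + 2)/22 = 7.36 | −0.64 | −44/22 = −2.00 |

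**Over the whole assumed range.** Mean stay falls by 0.24 days (n = 25, L = 8, k = 1, d = 2: 6/25) to 1.23 days (n = 22, L = 10, k = 3, d = 1: 27/22). DAOH falls by 0.80 days (n = 25, L = 10, k = 1: 20/25) to 3.00 days (n = 22, L = 8, k = 3: 66/22). The same deaths therefore move two listed safety outcomes in opposite directions.

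**Dependence on timing.** The stay shortens only when d < L. One in-hospital death on day 20 gives (21×8 + 20)/22 = 8.55 days, a rise.

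**ICU stay.** The same formula applies with L as the survivors' ICU stay, which the article does not give. For one day-1 death among 22 and L between 1 and 8 days, raw mean ICU stay falls by (L − 1)/22, between 0 and 0.32 days. ICU-free days to day 30, with death scored 0, would fall by (30 − L)/22, between 22/22 = 1.00 and 29/22 = 1.32 days. The raw measure is flat or looks favourable; the companion shows the harm.

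**The case against.** A reader might infer that the plan takes no account of death. It does not support that reading. Death to POD-30, DAOH and ventilator-free days are in the same list as the durations, and DAOH has its own interval method and is the example given for a histogram. An excess of early deaths would be counted directly and would lower DAOH.

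A reader might also infer that the missing rule for scoring deaths within a duration is an error. That is not supported either. Such rules, including how death enters ventilator-free days, are commonly left to the full protocol or SAP, which are not shown. That a day-1 death contributes one day is the plain reading of a duration, not something the article states.

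Three further points stand:

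- Recruitment, platelet supply and adherence alone decide progression, so no decision turns on these durations.
- The bias does not always favour the arm with more deaths, since a late in-hospital death lengthens the mean.
- Nothing in the article makes length of stay a criterion for non-inferior safety in the definitive trial, and ICU-free days could still be derived then.

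These points limit the importance of the concern. They do not give ICU stay a companion, and which outcomes are listed is settled in this article. Choosing the measure before outcomes are seen by arm is also better than redefining it afterwards.

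**Conclusion.** The point holds in a limited form. Raw ICU stay, hospital stay and ventilation time are safety outcomes summarised as differences in means, so an early death can read as a favourable short stay. For hospital stay and ventilation the list already supplies companions. For ICU stay it does not.

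The size is small: about a third of a day of hospital stay per day-1 death in an arm of 22, on an assumed 8-day survivor stay. It rests on assumed stays and deaths and on durations ending at death. Its reach is the pilot's descriptive safety reporting and any carry-over into the definitive trial. It is a minor improvement to the outcome list and does not affect the feasibility conclusions.

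**What to change.** - Add ICU-free days to POD-30, with death by POD-30 scored 0, as the between-arm ICU safety measure.
- Name the already listed ventilator-free days and DAOH as the between-arm measures for ventilation and hospital stay.
- Keep the raw durations for all patients as descriptive resource-use measures, which also serve the case-costing outcome, with the number of deaths per arm beside them.
- Do not compare arms on durations among survivors only. That conditions on an event after randomization and loses its protection.

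The cost is a change of outcome wording and one derived variable. Table 1 already schedules ICU stay and mortality, so no new data collection is needed.
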